## Abstract

**Background:**

Prostate cancer is the most commonly diagnosed cancer in men in developed countries. Androgen deprivation therapy (ADT) is a systemic treatment shown to increase survival in selected patients with prostate cancer. The use of ADT continues to increase for all stages and grades of prostate cancer despite known treatment-induced adverse effects. The primary aim of this study is to examine the efficacy of a targeted, multi-component resistance and impact-loading exercise programme together with a daily protein-, calcium- and vitamin D-enriched supplement on bone health in men treated with ADT for prostate cancer. Secondary aims are to determine the effects of this intervention on measures of total body and regional body composition, cardiometabolic risk, inflammatory markers, health-related quality of life and cognitive function.

**Methods:**

This study is a two-arm randomised controlled trial. Men currently treated with ADT for prostate cancer will be randomised to either a 52-week, community-based, exercise training and nutritional supplementation intervention (*n* = 51) or usual care control (*n* = 51). Participants will be assessed at baseline, 26 weeks and 52 weeks for all measures. The primary outcome measures are proximal femur and lumbar spine areal bone mineral density (BMD). Secondary outcomes comprise: changes in tibial and radial bone structure and strength, total body and regional body composition, muscle strength and function, as well as cardiometabolic health, catabolic/inflammatory and anabolic/anti-inflammatory cytokines, health-related quality of life and cognitive function.

**Discussion:**

This study investigates whether a multi-component intervention incorporating a targeted bone and muscle-loading programme in combination with a protein-, calcium- and vitamin D-enriched supplement can ameliorate multiple adverse effects of ADT when compared to usual care. The results will contribute to the development of exercise training and nutrition guidelines for optimising overall health in men treated with ADT for prostate cancer.

**Trial registration:**

Australia New Zealand Clinical Trial Registry (ANZCTR), ID: ACTRN12614000317695. Registered on 25 march 2014.

**Electronic supplementary material:**

The online version of this article (doi:10.1186/s13063-017-2185-z) contains supplementary material, which is available to authorized users.

## Background

In Australia, as in other developed countries, prostate cancer (PCa) is the most commonly diagnosed cancer in men [1]. Approximately 1.1 million new cases of PCa are diagnosed worldwide each year [1]. In Australia, a 2014 report estimated that approximately 13% of cancer-related deaths in men were attributed to PCa, which ranks second to lung cancer as the most common cause of cancer-related death in men [2]. Due to medical advancements in both the screening and treatment of PCa, 5-year relative survival rates of all PCa cases are now approaching 100% internationally [3], and thus these patients are living longer, but are susceptible to potential age-related and treatment-related declines in health. Therefore, the clinical paradigm is shifting to an increased focus on improving the quality of years lived.

Various modalities of androgen deprivation therapy (ADT), including those administered as neoadjuvant or adjuvant therapies with other treatments, are commonly used to treat PCa as it improves overall survival, particularly in men with advanced PCa [4–7]. However, the evidence that ADT prolongs survival in men with localised PCa remains limited and, therefore, debated [8, 9]. Despite this lack of evidence, the use of ADT continues to increase for all stages and grades of PCa [10]. It was estimated that approximately 23,500 Australian men received pharmacological ADT via gonadotropin-releasing hormone (GnRH) agonists in 2008–2009 [11]. After repeating this analysis for 2013–2014, we estimated that approximately 25,500 men are currently receiving ADT via GnRH agonists [12]. Thus, ADT remains the most common cause for severe hypogonadism in men in Australia.

Despite benefits in overall survival in appropriately selected men, the hypogonadism induced via ADT has been associated with numerous adverse effects, particularly with regard to musculoskeletal and cardiometabolic health. It has been reported that within the first 3 to 12 months of ADT, men experience a rapid and dramatic loss in bone mass (up to 11%) and concomitant losses in muscle mass (2–5%) [13–17] which may explain the observed 23–65% increased fracture risk in this group [18–20]. There is also a profound gain (up to 15%) in fat mass (FM) which likely contributes to the 10–45% reported increased risk of diabetes, coronary heart disease, myocardial infarction and sudden cardiac death [13, 17, 21–25]. Thus, there is a need to develop safe and effective interventions to manage the multiple treatment-induced adverse effects of ADT in men with PCa.

Exercise training has been strongly suggested as a viable intervention to ameliorate many of the adverse effects of ADT [17, 26–28]. In terms of musculoskeletal health outcomes, a number of interventions have shown that progressive resistance training (PRT) can increase muscle strength [29–33], muscle endurance [30, 34] and balance [30] in men treated with ADT. While there is also some evidence that PRT can improve or preserve lean body mass (LBM) [30, 32, 33, 35], a systematic review found that there was inconclusive findings on the effects of exercise training in men treated with ADT on bone health [26]. To date, only four studies have examined the efficacy of exercise training on areal bone mineral density (aBMD) in ADT-treated men, three of which were conducted over interventional periods of no longer than 20 weeks and observed no benefit [32, 36, 37]. This is perhaps not unexpected given that the typical bone remodelling cycle and new steady state that is measurable takes 6–8 months to complete, and thus it is unlikely that any true physiological skeletal adaptations would occur prior to this period. However, a recent 12-month randomised controlled trial (RCT) also reported no marked skeletal benefits of a targeted PRT and impact-loading exercise programme in men treated with ADT [36]. This may be due to a number of factors. First, the sample size of approximately 25 per group was below the target sample which may have limited the power to detect any between-group differences. Second, the impact exercise programme was non-progressive and only consisted of two-footed jumps (plus 10% body weight), and thus did not incorporate diverse loading patterns which are known to be important for bone remodelling. Third, the mean calcium intake was < 750 mg/day, well below the recommended dietary intake of 1200 mg/day. There is some evidence that insufficient calcium intakes can attenuate the skeletal responses to exercise in older adults [38]. Finally, this study was limited to an assessment of aBMD by dual-energy X-ray absorptiometry (DXA), which provides no information on other determinants of bone strength (e.g. trabecular volumetric BMD (vBMD), cortical structure), which may change following exercise training, independent of aBMD. This is important because the findings from a prospective study using high-resolution, peripheral, quantitative computed tomography (pQCT) found that treatment with ADT for 12 months was associated with losses of up to 11.3% in cortical and 3.5% in trabecular vBMD, which are two- to three-fold greater than changes observed in DXA aBMD [14]. In healthy older men, the findings from an 18-month RCT found that a targeted and progressive multi-component exercise programme incorporating PRT and a diverse range of weight-bearing, impact activities was safe and effective for improving lumbar spine trabecular vBMD and femoral neck aBMD, cross-sectional area and strength as well as muscle strength, mass and size [39]. Further long-term RCTs are required to examine whether similar well-designed and progressive multi-component exercise programmes in combination with adequate nutrition can ameliorate bone and muscle loss in men treated with ADT for PCa.

Clinical guidelines for optimising bone health in men on ADT recommend calcium and vitamin D treatment [11]. While direct evidence from RCTs to support their role in preventing bone loss in this group is lacking, a review based on secondary analyses of clinical trials reported that treatment with 500–1000 mg/day of calcium and 200–500 IU/day of vitamin D in ADT-treated men was inadequate to prevent bone loss [40]. In healthy older adults, there is level-1 evidence that calcium (>1000 mg/day) plus vitamin D (> 800 IU/day) can reduce fracture risk [41]. Studies have also shown that 2000 IU/day of vitamin D can improve muscle strength and function [41, 42], and that daily consumption of calcium-vitamin D fortified milk for 2 years prevented aBMD loss at multiple sites in healthy men aged older than 50 years [43]. While a systematic review and meta-analysis of prospective studies reported that increased dairy or calcium intake was associated with an increased risk of PCa, no association was observed with supplemental or non-dairy calcium, which suggest that other components of dairy rather than fat and calcium may increase PCa risk [44]. In line with these mixed findings, supplementation at doses < 1500 mg/day have been shown to either have no influence on PCa progression [45], reduce PCa risk [46] or decrease PSA velocity [47]. In addition, in men diagnosed with PCa, total milk/dairy intake after diagnosis was not associated with a greater risk of lethal PCa, with evidence of a decreased risk in those with a high intake of low-fat dairy [48].

There is also evidence that increased dietary protein in older adults can have favourable effects on both health, particularly when combined with calcium and vitamin D at recommended levels [38]. This has been attributed to several factors: a higher protein intake can increase serum insulin-like growth factor-1 (IGF-1), enhance intestinal calcium absorption, suppress parathyroid hormone levels as well as increase muscle mass and strength, which may improve bone health via increased loading on bone [49]. There is also evidence in older adults without PCa that higher protein intakes (> 1.2 g/kg) can enhance weight loss, offset muscle loss, improve lipid profiles and insulin sensitivity [50]. While this is not a universal finding, this could be explained by the modest level of protein intake achieved in some studies and/or the type (quality) of protein consumed. Currently there are no guidelines with regard to dietary protein for men with PCa using ADT.

It is well known that PRT stimulates muscle protein synthesis (MPS), but in a fasted state it also accelerates muscle protein breakdown (MPB) [51]. Ingestion of a high-quality, rapidly digested, protein-rich source, such as whey-protein, post-exercise can attenuate the increase in MPB and stimulate MPS to enhance the anabolic benefits of PRT [51]. Thus, combining PRT with whey-protein ingestion may represent an optimal strategy to enhance muscle hypertrophy. While questions still remain in terms of the optimal dose of protein needed to elicit a synergistic response with PRT, emerging evidence indicates that 20–40 g of high-quality protein be consumed early after a bout of PRT to enhance muscle mass and/or strength [51]. Moreover, Hanson et al. [52] recently demonstrated that consumption of 40 g of whey-protein alone, or following a single session of unilateral knee extension exercises, increased MPS beyond basal rates in men treated with ADT; albeit these increments were suboptimal when compared to healthy, age-matched men. However, a critical, but as yet unanswered, question is whether ingestion of a whey-protein-, vitamin D- and calcium-enriched drink with PRT can improve the multiple musculoskeletal health outcomes in ADT-treated men.

Therefore, the primary aim of this 12-month RCT is to determine whether a multi-component exercise programme targeting muscle and bone health combined with a protein-, calcium- and vitamin D-enriched drink can enhance hip and lumbar spine aBMD in men with PCa currently treated with ADT. The secondary aims are to examine the effects of the intervention on tibial and radial bone structure and strength, total body and regional body composition, muscle strength and function, as well as cardiometabolic health, catabolic/inflammatory and anabolic/anti-inflammatory cytokines, health-related quality of life (HR-QoL) and cognitive function.

## Methods

### Study design

This will be a 52-week, single-blinded, two-arm RCT consisting of a supervised and structured multi-component exercise programme in combination with a daily nutritional supplement. Men treated with ADT will be randomised to either an intervention consisting of a multi-component exercise programme and a daily protein-, calcium- and vitamin D-enriched supplement (*n* = 51) or a usual care control group (*n* = 51). Men allocated to usual care will not receive a placebo drink as typical ingredients used to develop a placebo drink (e.g. maltodextrin as a food additive) have the potential to alter blood glucose levels and muscle mass. A factorial 2 × 2 trial will not be conducted for several reasons: (1) the large sample size that would be required to detect an interaction and (2) findings from previous research in older adults which indicates that the benefits of exercise training on musculoskeletal health require adequate nutrition (e.g. dietary calcium > 1000 mg/day) [38]. This study will not evaluate whether the combination of protein, calcium and vitamin D with exercise training is more effective than either of these treatments alone, but will determine if combining the two approaches is effective for improving multiple health outcomes. This trial will be managed by the Institute for Physical Activity and Nutrition at Deakin University. The study has been approved by the Human Research Ethic Committees at Deakin University (HREC 2013-184) and Alfred Health (Project No: 455/15) and is registered with the Australian and New Zealand Clinical Trials Registry (ACTRN12614000317695). A summary of trial resgistration data and compliance with SPIRIT guidelines are shown in Additional files 1 and 2, respectively.

### Participants

Eligible participants will be men aged 50–85 years who are currently treated with ADT for histologically diagnosed PCa. Treatment with ADT must be pharmacological (surgical orchiectomy excluded) and administered for longer than 12 weeks at enrolment. Participants will be excluded if they do not have the ability to complete surveys in the English language, have any disorder known to affect bone, calcium or vitamin D metabolism (other than hypogonadism), are currently receiving pharmacological intervention known to affect bone metabolism (other than ADT), have supplemented with protein, calcium (> 600 mg/day) or vitamin D (> 1000 IU/day) in the past 3 months, have undertaken PRT (more than one session/week) or regular weight-bearing, impact exercise (> 150 min/week) in the past 3 months, are current smokers, have a weight greater than 159 kg, have plans to travel for longer than 6 weeks continuously within the following 52 weeks or have any absolute contraindications to exercise training (e.g. musculoskeletal, cardiovascular or neurological disorders) according to the American College of Sports Medicine guidelines [53].

### Recruitment and screening

Participants will be recruited via direct referral from clinicians across various hospitals, private practices and health networks in combination with promotion via PCa support groups and advertisements in state/local newspapers within Melbourne and surrounding areas in Victoria, Australia. The direct referral process will include mass mail-outs to potential participants and face-to-face discussions during regular consultations with physicians/specialists. PCa support groups will be initially contacted via email with information regarding the study, with an option to provide a brief presentation to groups interested. All potential participants will be screened initially via telephone to determine their eligibility based on the criteria outlined above. All eligible participants will be required to obtain medical approval from their physician and provide informed consent before participating in the study.

### Randomisation and blinding

Randomisation will be at the level of the individual participant following baseline testing, stratified by age (< 65 or ≥ 65 years) and Body Mass Index (< 30 or ≥ 30 kg/m^2^), using a computer-generated, random number sequence by an independent researcher. Due to limited funding, neither the participants nor researchers involved in the testing will be blinded to the group allocation, with the exception of the DXA and pQCT scans which will be assessed independently. A flow diagram of the study protocol is outlined in Fig. 1.

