### Measurements

All measures will be collected at baseline, 26 and 52 weeks. Additionally, 24-h food recalls will also be administered at 13 and 39 weeks to monitor any habitual fluctuations in dietary factors. With the exception of blood samples, 24-h food recalls and questionnaires, all data will be collected at Deakin University. Blood samples will be collected at an external commercial pathology clinic. The 24-h food recalls will be administered via telephone. Questionnaires will be completed by participants at home prior to each testing sessions (i.e. baseline, 26 and 52 weeks) and checked by the research staff during these face-to-face testing sessions. A summary of the proposed outcome measures is shown in Table 2. All participants will undergo all measures expect those specific to treatment allocation (i.e. compliance to the intervention). All data collected will be in a continuous format, aside from the outcomes from some of the questionnaires, which will be categorical in nature.

**Table 2 Tab2:** Summary of data collection

Variables	Data collection method	Data collection points		
		Baseline	26 weeks	52 weeks
Primary outcome measures				
Areal bone mineral density	DXA proximal femur and lumbar spine	x	x	x
Secondary outcome measures				
Bone structure and strength	pQCT scan at 4% and 66% radial and tibial site	x	x	x
Body composition	DXA total body and regional lean mass, fat mass and % body fat	x	x	x
	pQCT 66% radial and tibial muscle cross-sectional area and muscle density	x	x	x
Muscle strength	Chest press, leg press and seated row	x	x	x
	Grip strength	x	x	x
Functional capacity	30-s sit-to-stand	x	x	x
	Timed-up-and-go with cognitive task	x	x	x
	Four-square step test	x	x	x
	Berg balance scale	x	x	x
	Four-metre usual walk	x	x	x
	400-metre walk	x	x	x
Biochemistry and lipids	Overnight, fasted serum and plasma collection	x	x	x
Inflammatory markers	Overnight, fasted serum and plasma collection	x	x	x
Blood pressure	Automated measurement	x	x	x
Cognitive function	CogState Brief Battery computerised tests	x	x	x
	Rey Auditory Verbal Learning Test	x	x	x
	Trail Making Test (Part A and B)	x	x	x
	Digit Span Test	x	x	x
	National Adult Reading Test	x		
Health-related quality of life, fatigue and mood	Functional Assessment of Cancer Therapy-Fatigue questionnaire	x	x	x
	Functional Assessment of Cancer Therapy-Prostate questionnaire	x	x	x
	Assessment of Quality of Life 8D questionnaire	x	x	x
	Geriatric Depression Scale questionnaire	x	x	x

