### Primary and secondary outcome measures

The primary outcome for this study will be changes in proximal femur and lumbar spine aBMD. Secondary outcomes will comprise: changes in 4% and 66% tibial and radial vBMD, bone structure and strength, total body and regional body composition, muscle strength, functional capacity, cardiometabolic health, inflammatory biomarkers, HR-QoL and cognitive function.

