### Sample size calculation

The sample size calculations are based on our previous research in healthy and ADT-treated men. The mean (standard deviation (SD)) annual loss in femoral neck, hip and spine BMD in ADT-treated men was 3.0% (4.5), 2.6% (2.8) and 3.9% (3.0), respectively [14]. Our previous exercise trials in healthy older men have shown that 12 months of training can increase spine aBMD by 1.5–2.0% (SD 2.9) and hip aBMD by 1.2–1.8% (SD 2.8) [39, 55]. We estimate a conservative net difference in aBMD in favour of the intervention of ~ 3.5–4.0% at the hip and spine. Based on these estimates, 29 men in each group will provide 90% power (*P* < 0.05, two-tailed) to detect a difference of this magnitude (assuming a SD of 4.0). A net benefit of this magnitude is clinically relevant as there is evidence that a 1–2% gain in aBMD translates into a 7–14% reduction in fracture risk [36, 93]. For pQCT bone measures, radial and tibial cortical area decreased by 11.5% (8.8) and 12.5% (7.4), respectively, over 12 months in ADT-treated men [14]. While few long-term trials have examined the effect of exercise training on pQCT bone geometry in older men, several intervention trials in older adults have shown that a targeted, weight-bearing, impact-exercise programme can have beneficial effects on cortical bone [94, 95]. Assuming that the proposed intervention can half the rate of loss in cortical area, we estimate that we will require 39 men per group (SD 8.0; 90% power, two-tailed, *P* < 0.05). Based on a previous study and a meta-analysis showing that ADT is associated with an average 7.7% gain in fat and a 2.8% loss in lean mass over 3–12 months [96, 97], and that exercise training can prevent the gain in FM and increase (1–5%) or preserve LBM relative to usual care in men on ADT [30, 32], we estimate a sample size of 24–32 in each group will be required to observe a preservation in LBM and FM in the intervention group vs. usual care (90% power, two-tailed, *P* < 0.05). Assuming a conservatively projected 30% dropout, an estimated sample size of 51 men per group (102 in total) will be required. Based on previous studies in ADT-treated men focussing on a number of our secondary outcomes [32, 37, 98], we estimate that we will have sufficient power (80–90%, *P* < 0.05, two-tailed) to detect the following intervention effects: 20–40% for muscle strength; 8–22% for functional capacity; 4 points for fatigue (FACT-F), 15% for fasting plasma glucose and 14% for serum IL-6 and 20% for CRP. We will also have sufficient sample to detect a clinically meaningful difference of 0.5 SD in the Assessment of Quality of Life 8D questionnaire (AQoL-8D) and 9 points on the FACT-P (disease-specific QoL).

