
### Statistical analysis

Primary analyses will be conducted on an intention-to-treat basis using STATA statistical software (STATA, College Station, TX, USA). Per-protocol analysis will also be performed by including all participants who are at least 66% compliant to the exercise (two of three sessions per week) and 80% compliant to taking the supplements. Initially, descriptive statistics will be computed to compare the intervention and usual-care groups on background variables and baseline measures. All data will be screened for outliers and the normality of the distribution of all data will be assessed using Kolmogorov-Smirnov tests, with skewed data log transformed prior to analysis. Linear mixed models with random effects will be used to evaluate the effects of the intervention compared to usual control. Potential covariates to be included will be: age, duration of ADT use, other chronic conditions, change in medication and change in habitual physical activity or diet. Where possible, we will obtain endpoint measures from all withdrawals and include all randomised subjects in the final analysis. For participants who are lost to follow-up, missing data will be handled with multiple imputation, with subsequent sensitivity analyses to evaluate the effect of potential non-random attrition. Baseline measures and changes in outcome variables will be presented as means ± SD or 95% confidence intervals. A significance level of *P* < 0.05 will be adopted for all statistical tests.

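### Randomisation is stratified by age and BMI, but the stated covariate list omits BMI and leaves age optional, so the analysis does not commit to the strata used in the design

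*Protocol article*

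**What the plan says.** Under Randomisation and blinding, allocation is "stratified by age (< 65 or ≥ 65 years) and Body Mass Index", with BMI cut at 30 kg/m². This gives four age-by-BMI cells. The section does not mention blocks or any other device that forces equal numbers within a cell.

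Under Statistical analysis, "Linear mixed models with random effects will be used to evaluate the effects of the intervention compared to usual control". The covariates follow: "Potential covariates to be included will be: age, duration of ADT use, other chronic conditions", and then changes during the trial in medication and in activity or diet. BMI is not named. Age is named, but only as a candidate, and without saying whether it would enter as the stratum or in years.

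Two other statements bear on the role of baseline. Under Measurements, "All measures will be collected at baseline, 26 and 52 weeks". Under Primary and secondary outcome measures, "The primary outcome for this study will be changes in proximal femur and lumbar spine aBMD".

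**The concern.** A factor chosen for stratification is one the designers thought worth balancing, and the usual rule is that the analysis then includes it. Here the article names five groups of covariates, among them variables that arise after randomisation, yet leaves out one of the two factors used to allocate men and does not commit to the other.

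Two things are at stake, both modest:

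- **Precision.** If the strata predict change, their variation stays in the error term and confidence intervals are wider than they need be.
- **Calibration.** If the arms are also balanced within strata, the unadjusted standard error overstates the real sampling variation, and the test rejects a true null less often than 5%.

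Neither produces bias or an excess of false positives.

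**Working it through.** **Inputs from the protocol article (Sample size calculation).** Difference 3.5 percentage points (the lower end of "net difference in aBMD in favour of the intervention of ~ 3.5–4.0% at the hip and spine"), SD 4.0, two-sided 0.05, 90% power, 29 per group; 51 randomised per group with 30% dropout.

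**Assumed, because not given.** R², the share of the variance of change explained by the omitted strata; r, the correlation of baseline with follow-up.

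**1. The plan's own figure.** n = 2(1.960 + 1.282)² × 4.0² / 3.5² = 27.5, so 28 per group by the normal approximation. The noncentral t gives 29. The stated figure reproduces as a plain two-sample comparison of change with no covariates.

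**2. Precision.** The unadjusted SE divided by the adjusted SE is 1/√(1 − R²). At 29 per group the unadjusted SE is 4.0 × √(2/29) = 1.050.

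| R² | Unadjusted SE too large by | Adjusted SE, 29 per group | Normal-approximation n for 90% power | Power at 29 per group |
|---|---|---|---|---|
| 0 | 0% | 1.050 | 28 | 91.5% |
| 0.05 | 2.6% | 1.024 | 27 | 92.8% |
| 0.10 | 5.4% | 0.997 | 25 | 94.0% |

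**3. Test level if arms are balanced within strata.** Actual level = 2 × [1 − Φ(1.96/√(1 − R²))]. This is 4.4% at R² = 0.05 and 3.9% at R² = 0.10.

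A simulation with stratified blocks and 70 completers (51 × 0.7 = 35.7, about 35 per arm) agrees:

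- At R² = 0.10 the mean reported SE was 0.954 unadjusted and 0.904 adjusted. The actual spread of the estimates was 0.913 and 0.912. Under balance, then, the unadjusted estimate is about as precise as the adjusted one, but its reported SE is too large. Rejection under the null was 4.0% unadjusted and 5.2% adjusted.
- At R² = 0 adjusting cost almost nothing: SE 0.951 against 0.952, rejection 4.7% and 4.8%.

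**4. How the strata must enter.** Take a three-visit random-intercept model with an assumed between-man SD of 15 and an SD of change of 4 (residual variance 8, since √(2 × 8) = 4). With 35 per arm, the SE of the 52-week group-by-time contrast is √(2 × 16/35) = 0.956. Adding BMI as a main effect that explains 10% of the between-man variance leaves it at 0.956. A main effect shifts a man's level at every visit and cancels out of his change. The strata help only where they are allowed to act on change.

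**5. Baseline.** With equal variances at the two visits, the SE of a raw change score divided by the SE adjusted for baseline is √(2/(1 + r)). The excess is 15% at r = 0.5, 8% at 0.7, 2.6% at 0.9 and 0.5% at 0.98. In the mixed model of step 4 (r = 225/233 = 0.97), giving both arms a common baseline mean lowers the SE from 0.956 to 0.948, or 0.9%.

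**The case against.** The strongest reply is that this is a condensed article, that its list is expressly provisional, and that the final model belongs in an analysis plan which is not shown. Nothing says BMI will be excluded. That holds for detail such as how age is coded. It does not fully answer the point, because the article does give a list, and that list does not follow the allocation scheme the same article describes.

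Several stronger readings are tempting, and the document does not support them:

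- **That baseline is left out.** It is missing from the covariate list only. With three visits, a mixed model and change as the primary outcome, baseline may enter as the first repeated response. What can be said is that its role is not stated.
- **That standard errors are wider as a matter of fact.** This needs strata that predict change in areal bone mineral density (aBMD), and the article gives no evidence either way.
- **That the true error rate is 4.4% or 3.9%.** This also needs balance within strata, which the article does not describe. With unblocked allocation within strata the unadjusted test keeps its level, and only the loss of precision remains.
- **That the trial is underpowered as a result.** The calculation never relied on covariates. At 35 completers per arm, unadjusted power for 3.5 points with SD 4.0 is 95.5%.
- **That duration of ADT must become a fixed covariate.** That may be sensible on prognostic grounds, but it does not follow from the stratification.

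**Conclusion.** The mismatch is real and limited. The article stratifies on two factors and commits its models to neither; one of them, BMI, is not named at all. The likely consequence is a small loss of precision: nothing at R² = 0, about 2.6% on the standard error at 0.05 and about 5.4% at 0.10. A slightly conservative test follows only if allocation was also balanced within cells. These R² values are assumptions. If age is in fact included, only what BMI adds counts towards R².

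The gain from conditioning on baseline is small for aBMD, where the correlation is probably high. It would be larger for less correlated secondary outcomes if these were otherwise analysed as raw change. The primary conclusion is unlikely to turn on any of this. The case for the change is that it aligns analysis with design at almost no cost.

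**What to change.** In the Statistical analysis section, state that:

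- every primary and secondary model includes the age stratum (< 65, ≥ 65) and the BMI stratum (< 30, ≥ 30) as prespecified terms, whatever is decided about the other covariates;
- they enter so that they act on change: stratum-by-visit terms in a repeated-measures model, or stratum covariates in a model of change from baseline;
- the model conditions on the baseline value of the outcome, either as a covariate or through a common baseline mean across arms.

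No new data are needed: age, BMI and the baseline outcomes are already collected. The cost is wording and a few degrees of freedom. That is two parameters in a model of change with additive strata. With baseline as a response it is six: two main effects plus two factors × two follow-up visits.
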